### Blinding

All treatments across the three groups will be carried out by a single operator, who will have completed training and calibration sessions during the initial phase of the study. Clinical assessments after 48 hours as well as four, eight and twelve months after treatment (follow-up) will be performed by an examiner blinded to allocation (single-blind study). The operator and examiner will undergo previous calibration exercises, evaluating approximately 20 cases, with the calculation of the Kappa statistic to ensure greater than 85% inter-observer agreement. The calibration will follow the criteria of the modified index of the United States Public Health Service (USPHS) [24,25] and the MIH-SSS diagnostic criteria [20]. The data will be analyzed by a blinded statistician.

### Interventions

#### Photobiomodulation.

Photobiomodulation will be performed with a low-power infrared diode laser (DMC, São Carlos, Brazil) in a single session. The laser will be administered at three points in contact and perpendicular to the surface on the vestibular mesial and distal cervical thirds as well as the center of the occlusal face [26]. Each point will be irradiated for 30 seconds with an energy of 3 J. The photobiomodulation parameters are described in Table 1.

**Table 1 pone.0329641.t001:** Photobiomodulation parameters.

Photobiomodulation parameters	
Application method	Contact
Number of points irradiated	3
Number of sessions	1
Wavelength (nm)	808 ± 10
Irradiance (mW/cm^2^)	3571
Spectral width (FWHM)	4.8 ± 2 nm
Operating mode	Continuous
Power	100 mW
Beam type	Multi-mode
Beam area [cm^2^]	0.028
Total exposure time	30 s
Radiant exposure [J/cm^2^]	35.7
Energy per point [J]	1
Total energy [J]	3

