### Clinical protocol

#### Group 1 – photobiomodulation + restoration with self-cure composite resin.

Initial periapical radiograph;Hypersensitivity reading (Wong-Baker Faces Pain Rating Scale for subjective pain of volunteer and SCASS for examiner’s assessment);Application of photobiomodulation;Relative isolation (lip bumper, cotton roll and aspirator);Selective removal of carious tissue with excavator, which involves complete removal of carious dentin from the surrounding walls followed by partial removal of softened dentin from the pulp wall (only Code 6 of MIH-SSS criteria);Cleaning with cotton and water;Application of primer (Stela; SDI, Melbourne, Vic, Australia) on dentin and/or enamel, wait 5 seconds;Application of mild compressed air on adhesive for 3 seconds;Restoration with self-cure composite resin (Stela; SDI, Melbourne, Vic, Australia) extending to adjacent demarcated opacities;Clinical follow up after 48 hours and at four-month intervals for a period of 12 months (modified USPHS index);Hypersensitivity reading after 48 hours and at four-month intervals for a period of 12 months (Wong-Baker Faces Pain Rating Scale for subjective pain of volunteer and SCASS for examiner’s assessment).

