#### Group 3 – photobiomodulation + restoration with bulk-fill composite resin.

Initial periapical radiograph;Hypersensitivity reading (Wong-Baker Faces Pain Rating Scale for subjective pain of volunteer and SCASS for examiner’s assessment;Relative isolation (lip bumper, cotton roll and aspirator);Application of photobiomodulation;Selective removal of carious tissue with excavator, which involves complete removal of carious dentin from the surrounding walls followed by partial removal of softened dentin from the pulp wall (only Code 6 of MIH-SSS criteria);Selective etching of enamel adjacent to demarcated opacities with 35% phosphoric acid (Ultra Etch; Ultradent, Indaiatuba, SP, Brazil) for 20 seconds;Active application of universal adhesive (Ambar; FGM, Joinville, SC, Brazil) on dentin and enamel for 20 seconds (repeat procedure);Application of mild compressed air on adhesive for 5 seconds;Photoactivation for 10 seconds, peak of 1200 Mw/cm^2^ (Radii Cal; SDI, Melbourne, Vic, Australia);Restoration with Tetric N Ceram bulk-fill composite resin (Tetric N Ceram Bulk Fill; Ivoclar Vivadent, Barueri, SP, Brazil) with increments up to 4 mm, extending to demarcated opacities;Photoactivation for 20 seconds (Radii Cal; SDI, Melbourne, Vic, Australia);Clinical follow up after 48 hours and at four-month intervals for a period of 12 months (modified USPHS index);Hypersensitivity reading after 48 hours and at four-month intervals for a period of 12 months (Wong-Baker Faces Pain Rating Scale for subjective pain of volunteer and SCASS for examiner’s assessment).

The interventions will begin without an initial application of local anesthesia. The children will be informed that anesthesia is available and can be administered at any time during the procedure, if necessary.

A children’s toothpaste with 1100 ppm fluoride, which does not contain any components specifically designed for treating dentin hypersensitivity, will be provided to all participants. This toothpaste will be used for daily oral hygiene during the study to ensure consistency across all participants and avoid any confounding factors related to hypersensitivity treatment.

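### The text and Table 1 give photobiomodulation doses that differ three-fold (3 J against 1 J per point), and the article does not say which governs

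*Protocol article*

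**What the plan says.** The protocol article specifies the laser dose twice, both times under Interventions, Photobiomodulation.

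- **Text.** "The laser will be administered at three points in contact and perpendicular to the surface", followed by "Each point will be irradiated for 30 seconds with an energy of 3 J". The time and the energy are both attached to each point.
- **Table 1.** The text continues: "The photobiomodulation parameters are described in Table 1". The table lists three points, one session, continuous mode, 100 mW, a beam area of 0.028 cm², an irradiance of 3571 mW/cm² and a radiant exposure of 35.7 J/cm². It has separate rows for energy per point (1 J) and total energy (3 J). The row "Total exposure time" reads 30 s.

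The step lists for Groups 1 and 3 under Clinical protocol say only that photobiomodulation is applied, without a dose. Group 2 follows the Group 1 sequence without that step. According to the Blinding section, "All treatments across the three groups will be carried out by a single operator".

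**The concern.** The same two numbers, 30 s and 3 J, appear per point in the sentence and as totals over three points in the table. Both cannot be right.

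Photobiomodulation is named in the primary objective and is the only step that separates Group 1 from Group 2. Its dose therefore defines what that contrast tests. The sentence is also a working instruction: an operator who follows it literally delivers three times the tabulated energy. The tabulated power would not expose the slip, because both versions can be delivered at 100 mW. From this article a reader could not say which dose produced the results, or repeat the treatment.

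**Working it through.** **Inputs**, all from the Photobiomodulation text and Table 1:

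- 3 points and 1 session; power 100 mW = 0.1 W, continuous; beam area 0.028 cm².
- Text: 30 s and 3 J at each point.
- Table 1: 1 J per point, 3 J in total, 30 s in total, 35.7 J/cm², 3571 mW/cm².

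**Formulas.** Energy = power × time. Irradiance = power / area. Radiant exposure = energy per point / area.

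**Step 1: reproduce Table 1.**

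- Irradiance: 100 / 0.028 = 3571 mW/cm².
- Time per point: 30 s / 3 = 10 s.
- Energy per point: 0.1 W × 10 s = 1 J.
- Radiant exposure: 1 / 0.028 = 35.7 J/cm².
- Total energy: 3 × 1 J = 3 J.

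Every row reproduces. Two separate routes give 10 s per point: 30 s / 3 points, and 1 J / 0.1 W. Dividing 35.7 J/cm² by 3.571 W/cm² also gives 10 s, but this is the second route again, because the area cancels.

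**Step 2: take the sentence as written.**

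- Energy per point: 0.1 W × 30 s = 3 J, so the sentence also fits the power.
- Radiant exposure: 3 / 0.028 = 107.1 J/cm².
- Total time: 3 × 30 s = 90 s. Total energy: 3 × 3 J = 9 J.

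**Step 3: compare.**

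| Quantity | Text | Table 1 | Ratio |
|---|---|---|---|
| Time per point | 30 s | 10 s | 3 |
| Energy per point | 3 J | 1 J | 3 |
| Radiant exposure per point | 107.1 J/cm² | 35.7 J/cm² | 3 |
| Total time | 90 s | 30 s | 3 |
| Total energy | 9 J | 3 J | 3 |

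The 10 s is derived, since Table 1 has no row for time per point. The other four quantities are rows of the table.

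**Step 4: try to reconcile them.**

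- 3 J per point in 10 s needs 3 / 10 = 0.3 W (300 mW), not 100 mW.
- 1 J per point in 30 s needs 1 / 30 = 0.033 W (33 mW), not 100 mW.
- Reading the table's 30 s as a time per point gives 0.1 W × 30 s = 3 J per point, against the table's own 1 J per point, 3 J in total and 35.7 J/cm².

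None of these works.

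**Step 5: children affected.** Two laser groups × 25 = 50 of 75.

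**The case against.** The best answer is that this is one badly worded sentence. Table 1 is coherent, the text sends the reader to it for the parameters, and the sentence's 30 s and 3 J are exactly the table's totals. The four conflicting rows are not four errors: with power, area and number of points fixed, they move together as one factor of three. Nothing is miscalculated either, since each version agrees with the 100 mW. Randomisation, sample size and analysis are untouched, and one trained operator treats every child.

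Most of that stands. It makes Table 1 the likelier intent and makes this a single contradiction. It does not settle the dose. The article does not say that the table overrides the sentence just before its citation, and it does not say that the operator's training covers the laser settings.

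Two further limits are fair. The article gives no threshold by which 35.7 or 107.1 J/cm² could be called safe or unsafe, so no claim of physical harm is made. The full protocol, cited under Study design as S2 File, is not shown here and may state the setting. That would show which version to correct, but the article would still contradict itself.

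**Conclusion.** The contradiction is real and must be fixed. The article gives two doses for its experimental component that differ by a factor of three: 3 J against 1 J per point, and 9 J against 3 J in total. Table 1 is probably what was meant, but that is inferred from the matching figures and not stated.

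The three-fold size rests on the tabulated 100 mW, 0.028 cm² and three points, which the two versions share. The conflict applies equally to Groups 1 and 3. If one setting is used throughout, it does not bias the comparison between groups; the damage is to correct delivery, dose reporting and replication.

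**What to change.** 1. Confirm the intended device setting with the sponsor, starting from S2 File.
2. If Table 1 is right (the likelier case), change the sentence to 10 s and 1 J per point, 30 s and 3 J in total.
3. If the sentence is right, change four rows of Table 1: 3 J per point, 107.1 J/cm², 90 s in total and 9 J in total.
4. Brief the operator, check the setting used for any child already treated, and report the dose actually given.

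The cost is almost nil: one sentence or four table rows, a short briefing and a check of treatment records.

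A minor editorial point, separate from the dose: the Group 1 list has "Application of photobiomodulation;Relative isolation (lip bumper, cotton roll and aspirator", while the Group 3 list has "Relative isolation (lip bumper, cotton roll and aspirator);Application of photobiomodulation". The same edit can put the two steps in one order.

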### Clinical protocol

#### Group 1 – photobiomodulation + restoration with self-cure composite resin.

Initial periapical radiograph;Hypersensitivity reading (Wong-Baker Faces Pain Rating Scale for subjective pain of volunteer and SCASS for examiner’s assessment);Application of photobiomodulation;Relative isolation (lip bumper, cotton roll and aspirator);Selective removal of carious tissue with excavator, which involves complete removal of carious dentin from the surrounding walls followed by partial removal of softened dentin from the pulp wall (only Code 6 of MIH-SSS criteria);Cleaning with cotton and water;Application of primer (Stela; SDI, Melbourne, Vic, Australia) on dentin and/or enamel, wait 5 seconds;Application of mild compressed air on adhesive for 3 seconds;Restoration with self-cure composite resin (Stela; SDI, Melbourne, Vic, Australia) extending to adjacent demarcated opacities;Clinical follow up after 48 hours and at four-month intervals for a period of 12 months (modified USPHS index);Hypersensitivity reading after 48 hours and at four-month intervals for a period of 12 months (Wong-Baker Faces Pain Rating Scale for subjective pain of volunteer and SCASS for examiner’s assessment).

#### Group 2 – restoration with self-cure composite resin.

Same as previous sequence (Group 1) with exception of Item 3.

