### Description of sample

Teeth will be selected from male and female children 6–10 years of age with no distinction as to ethnicity enrolled for outpatient treatment at the Aria College in the city of Brasília with first molars that have MIH and restorative treatment need. The study has received a letter of approval from Aria College, granting permission for the research to be conducted in the Department of Pediatric Dentistry at their facility. Individuals who met the eligibility criteria will immediately be randomized and treated. Each participant will receive treatment on a single molar affected by MIH. In cases where more than one tooth meets the eligibility criteria, the tooth to be included in the study will be selected randomly through a simple lottery method. This selection process will occur prior to the randomization of the interventions to ensure a clear and unbiased allocation of treatments. The trial will be reported following the CONSORT guidelines.

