#### Hypersensitivity assessment.

Pain perception in children was evaluated through the Wong-Baker Faces Pain Rating Scale [29] and the Schiff Cold Air Sensitivity Scale (SCASS) [30] will be used for the assessment of the operator and examiner. Following isolation of the neighboring teeth with gauze, compressed air will be applied to the tooth with MIH for three seconds. The SCASS is scored as follows: 0 (no reaction); 1 (no reaction, but patient reports discomfort); 2 (patient reacts and moves away from stimulus); and 3 (patient reacts and asks operator to stop) [3]. Hypersensitivity will be measured using the Wong-Baker Faces Pain Rating Scale and SCASS prior to the procedure, 48 hours after restorative treatment and at four-month intervals for the 12-month follow-up period.

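### Group 2 has no sham laser, so the only comparison that isolates photobiomodulation mixes the laser effect with expectation; a blinded baseline reading is also not secured

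*Protocol article*

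**What the plan says.** **Allocated procedures.** In the Protocol article, Clinical protocol, the Group 1 list starts with the radiograph (Item 1) and the hypersensitivity reading (Item 2). It continues "Application of photobiomodulation;Relative isolation (lip bumper, cotton roll and aspirator", so the laser is Item 3. Group 2 is "Same as previous sequence (Group 1) with exception of Item 3". The article describes no sham or inactive application.

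**Blinding.** The Blinding section covers "Clinical assessments after 48 hours as well as four, eight and twelve months after treatment (follow-up" and says that these "will be performed by an examiner blinded to allocation (single-blind study". It also blinds the statistician. It does not say that the child, the guardian or the operator is blinded, and one operator delivers all treatments. Baseline is not among the visits listed.

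**Outcome scales.** The Group 1 and Group 3 lists describe the reading as "Wong-Baker Faces Pain Rating Scale for subjective pain of volunteer and SCASS for examiner’s assessment". The Hypersensitivity assessment section instead says that SCASS "will be used for the assessment of the operator and examiner", without dividing the visits between them. Its score 1 is "1 (no reaction, but patient reports discomfort"; scores 2 and 3 require the child to react to the stimulus.

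**Timing.** Description of sample says "Individuals who met the eligibility criteria will immediately be randomized and treated". The Hypersensitivity assessment section puts the first reading before the procedure. The article does not say whether the envelope is opened before or after that reading.

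**The concern.** The primary objective is improvement of hypersensitivity, measured by pain scales in children aged 6 to 10. If children know whether they had the laser, those who did may report less pain because they expect to, or because they received more attention. That difference would be read as an effect of photobiomodulation. Blinding the examiner does not remove it, because it arises in the child before anything is scored.

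Baseline is a second, smaller matter. It is one of the five time points in the repeated measures ANOVA, yet the article does not establish that it is read by someone unaware of the allocation.

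**Working it through.** The plan gives no figure on this point, so the check is mainly a comparison of its sections.

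**1. Which pair isolates the laser?**

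| Pair | Laser differs? | Restorative system differs? |
|---|---|---|
| Group 1 vs Group 2 | yes | no |
| Group 1 vs Group 3 | no | yes |
| Group 2 vs Group 3 | yes | yes (resin, etching, adhesive, light curing) |

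Only Group 1 versus Group 2 differs by photobiomodulation alone. Group 1 versus Group 3 is not affected by the missing sham, since both groups receive the laser.

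**2. Can the child tell?** The Interventions section describes contact at three points. Its text gives 30 s per point, so 3 × 30 = 90 s. Table 1 gives 30 s total exposure and 1 J per point at 100 mW, so 1 J / 0.1 W = 10 s per point and 3 × 10 = 30 s. The text and the table disagree and must be reconciled. Under either, a child who had the step will have noticed it, and a guardian can learn of it from the child or by being present. This is an inference from the procedure, since the article is silent on what families are told.

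**3. What does the blinded examiner protect?**
- Wong-Baker: the child gives the rating. The examiner's ignorance of the group does not change what the child knows, so there is no protection.
- SCASS 1: depends on the child reporting discomfort, so it is exposed in the same way.
- SCASS 2 and 3: the examiner observes a reaction. Blinding prevents allocation-driven scoring of that behaviour, but the behaviour itself may still follow expectation. Protection is partial.

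**4. Is the baseline blinded?**
- Against: the visits listed under Blinding begin at 48 hours; the reading is printed inside each group's list; eligible children are randomized and treated at once; and one section names the operator, who delivers the treatment, alongside the examiner for SCASS.
- For: the reading precedes the laser in every group. The radiograph (Item 1) is also an exclusion check and hypersensitivity is an inclusion criterion, so a step's place in the list does not show that it follows randomization. The step lists give SCASS to the examiner.
- Result: the rater and the timing relative to the envelope are not fixed. The article shows neither a blinded nor an unblinded baseline.

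**5. Illustration of scale (the bias b is an assumption).** Take no true laser effect, n per group, a shift of b SD in the reported score, and an unadjusted two-sided 5% z test of Group 1 versus Group 2:

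P(reject) = Φ(b/√(2/n) − 1.96) + Φ(−b/√(2/n) − 1.96)

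For n = 25, √(2/25) = 0.283. At b = 0.3, b/√(2/n) = 1.061, and Φ(−0.899) + Φ(−3.021) gives about 0.19.

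| Assumed b (SD) | n = 25 | n = 22 |
|---|---|---|
| 0.1 | 6% | 6% |
| 0.2 | 11% | 10% |
| 0.3 | 19% | 17% |
| 0.5 | 42% | 38% |

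The planned Bonferroni adjustment would lower these rates but would leave the bias in the estimate. The table shows what a given shift would do; it is no evidence that a shift of any size will occur.

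**The case against.** The strongest reply is that the trial openly calls itself single-blind. The missing sham is then a disclosed design choice and not a contradiction, and the article condenses a fuller protocol. The first part stands: this is a limitation of the design, not an error of fact. The second does not remove the point, because the Group 2 sequence is stated explicitly and leaves no room for an inactive step. It does have force for the baseline, where the fuller protocol or the schedule figure may fix the timing.

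Three stronger readings are tempting but not supported:

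- **That the baseline is unblinded.** The article does not say when the envelope is opened, or that a child or guardian knows the group before Item 2. The step lists name the examiner for SCASS.
- **That a change of rater between baseline and follow-up biases the group comparison.** Even if the operator scored every baseline and the examiner every later visit, the switch would be common to all groups. A constant rater difference would fall into the time effect and largely cancel between groups. Bias would require the operator to score differently by known allocation, which is not shown.
- **That expectation would account for a definable share of the planned effect.** The sample size section gives one f of 0.352 across three groups and no planned pairwise difference, and no bias figure is given.

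A fair objection also concerns cost: ethics approval is dated December 4, 2024 and recruitment was planned from February 1, 2025. A sham introduced after enrolment starts would split Group 2 into two versions.

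**Conclusion.** The point holds for the missing sham. As planned, Group 1 versus Group 2 cannot separate the effect of photobiomodulation from expectation and attention on Wong-Baker, and can do so only in part on SCASS. This rests on the explicit Group 2 sequence, the stated scope of blinding, the definitions of the scales, and the inference that a child notices a contact laser. The direction one would expect favours the laser group, but the size cannot be estimated from the document.

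For the baseline, the conclusion is limited to this: blinding is not secured, and the sections on who scores SCASS do not agree.

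This should be changed because it bears on the primary outcome and the remedy is cheap. It does not invalidate the trial, and it leaves the comparison of Group 1 with Group 3 untouched.

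**What to change.** 1. **Sham in Group 2.** Apply the same handpiece at the same three points for the same time with emission off, and keep child and guardian unaware of which was used. Active treatment is unchanged. The cost is about 90 s of chair time for each of 25 children on the Interventions text (30 s on Table 1, until the two are reconciled), consent wording and a likely ethics amendment.
2. **If enrolment is too far advanced for this.** State in the protocol and the report that the Group 1 versus Group 2 pain comparison cannot separate the laser effect from expectation, and limit the conclusion accordingly. This costs only wording.
3. **Baseline.** State that the blinded examiner takes the baseline Wong-Baker and SCASS readings before the envelope is opened. The examiner must attend the treatment visit for the reading; no new staff are needed.
4. **SCASS rater.** Reconcile the Blinding section, the step lists in the Clinical protocol and the Hypersensitivity assessment section so that the operator does not score SCASS as an outcome.

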#### Group 3 – photobiomodulation + restoration with bulk-fill composite resin.

Initial periapical radiograph;Hypersensitivity reading (Wong-Baker Faces Pain Rating Scale for subjective pain of volunteer and SCASS for examiner’s assessment;Relative isolation (lip bumper, cotton roll and aspirator);Application of photobiomodulation;Selective removal of carious tissue with excavator, which involves complete removal of carious dentin from the surrounding walls followed by partial removal of softened dentin from the pulp wall (only Code 6 of MIH-SSS criteria);Selective etching of enamel adjacent to demarcated opacities with 35% phosphoric acid (Ultra Etch; Ultradent, Indaiatuba, SP, Brazil) for 20 seconds;Active application of universal adhesive (Ambar; FGM, Joinville, SC, Brazil) on dentin and enamel for 20 seconds (repeat procedure);Application of mild compressed air on adhesive for 5 seconds;Photoactivation for 10 seconds, peak of 1200 Mw/cm^2^ (Radii Cal; SDI, Melbourne, Vic, Australia);Restoration with Tetric N Ceram bulk-fill composite resin (Tetric N Ceram Bulk Fill; Ivoclar Vivadent, Barueri, SP, Brazil) with increments up to 4 mm, extending to demarcated opacities;Photoactivation for 20 seconds (Radii Cal; SDI, Melbourne, Vic, Australia);Clinical follow up after 48 hours and at four-month intervals for a period of 12 months (modified USPHS index);Hypersensitivity reading after 48 hours and at four-month intervals for a period of 12 months (Wong-Baker Faces Pain Rating Scale for subjective pain of volunteer and SCASS for examiner’s assessment).

The interventions will begin without an initial application of local anesthesia. The children will be informed that anesthesia is available and can be administered at any time during the procedure, if necessary.

A children’s toothpaste with 1100 ppm fluoride, which does not contain any components specifically designed for treating dentin hypersensitivity, will be provided to all participants. This toothpaste will be used for daily oral hygiene during the study to ensure consistency across all participants and avoid any confounding factors related to hypersensitivity treatment.

